### Outcomes

The primary outcome measure of this study will be quality of life, measured with the personalized and reliable, validated and responsive Patient-Reported Outcomes Measurement Information System – Physical Functioning (PROMIS-PF) item bank [20, 41, 42]. A list of 29 activities from the item bank will be presented to the patients at the baseline measurement, from which patients will be asked to select eight activities which are most relevant for them in daily life. By doing this, patients will design their own quality of life short form.

Each activity consists of five functioning levels. Seventeen of the 29 items are scored as: without any difficulty, with a little difficulty, with some difficulty, with much difficulty and unable to do. Twelve items are scored as: not at all, very little, somewhat, quite a lot, and cannot do. At baseline, patients will report their current functioning level. The personalized short form will also be presented to the patients during all follow-up measurements. Post-surgery, successful ‘return to an activity’ is defined by a return to an activity with at least one functioning level higher as compared to the baseline (pre-surgery) functioning level, for instance from ‘with much difficulty’ to ‘with some difficulty’. If patients reach this level, they will be asked at what day they reached this level. Our primary outcome will be defined as the time since surgery to resume six out of the selected eight activities of their own quality of life short form. The secondary outcomes that will be assessed are shown in Table 2.

**Table 2 Tab2:** Secondary outcomes

Return to work	The time (i.e. days, months) between the surgery and the first day back at work, both partly and fulltime
Knee Functioning, measured with The Knee Injury and Osteoarthritis Outcome Score (KOOS) [43]	The KOOS consists of 42 items that assesses five outcomes: pain (9), symptoms (7), activities of daily living (17), sport and recreation function (5), and knee-related quality of life (4) on a 5-point Likert scale (0, no problems – 5, extreme problems). Scores are transformed to a scale of 0 – 100, with 0 representing extreme knee problems and 100 representing no knee problems
Pain intensity, measured with the von Korff questionnaire visual analog scale (VAS) [44]	The pain VAS is a unidimensional measure of pain intensity and is widely used in postsurgical patient populations. This questionnaire measures the severity of pain on a scale of 0 (no pain) to 10 (extreme pain) and the associated impediment with daily life activities
Health-related quality of life, measured with the 5-level EuroQol-5d (EQ-5D-5L) [45]	The EQ-5D-5L contains five questions that represent the following health dimensions: mobility, self-care, usual activities, pain/discomfort and anxiety/depression. For each dimension, patients have to indicate the severity of their health complaints. There are five severity levels: normal/no problems, slight problems, moderate problems, severe problems, and extreme problems, all scored from 1 (no problems) to 5 (extreme problems). Hence, answers to these questions will represent a patient’s EQ-5D-5L health state, ranging from 11,111 (no problems on all dimensions) to 55,555 (extreme problems on all dimensions)
Physical difficulty experienced at work, measured with the Work, Osteoarthritis or joint-Replacement Questionnaire (WORQ) [46]	The WORQ is a valid and reliable questionnaire that can be used to assess the impact of the knee replacement. It contains 13 questions, each representing a physical activity (e.g. kneeling, crouching or standing). Patients have to grade how difficult this activity is to perform on a five-point scale: none, mild, moderate, sever of extreme – corresponding with scores of 4 to 0, respectively. The sum of scores is then converted into a score of 0 (worst score) to 100 (best score)
Fatigue, measured with the Multidimensional Fatique Inventory (MFI-20) [47]	The MFI-20 is a valid and reliable self-report instrument that has been designed to measure fatigue in several dimensions: general fatigue, physical fatigue, reduced activity, reduced motivation and mental fatigue. Each dimension has five questions rated on a five-point Likert scale. Scores on each subscale range from 4 to 20, with higher scores indicating greater fatigue. The sum of the subscale scores represents the total fatigue score (range 20 – 100), with a higher score indicating a higher level of fatigue

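### Activities already at the best level at baseline can never count as returned, so a patient with three or more of them among the eight cannot have the primary event

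*Protocol article*

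**What the plan says.** The endpoint is set out in the protocol article, Methods, Outcomes. From a list of 29, "patients will be asked to select eight activities which are most relevant for them in daily life". Relevance is the only stated criterion; an activity need not be limited at baseline.

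The scale is closed: "Each activity consists of five functioning levels". Its best category is the first one listed for each item type: "Seventeen of the 29 items are scored as: without any difficulty, with a little difficulty", and so on down; "Twelve items are scored as: not at all, very little, somewhat, quite a lot, and cannot do". At baseline the patient reports current functioning, which may be any of the five levels. The same eight items are presented at every follow-up.

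A successful return to one activity "is defined by a return to an activity with at least one functioning level higher as compared to the baseline (pre-surgery) functioning level". The primary outcome is "the time since surgery to resume six out of the selected eight activities of their own quality of life short form". Patients who reach the required level are asked on which day they did so.

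The article contains no rule for an activity already at the best level: no exemption, no replacement, no credit for regaining the baseline level.

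**The concern.** Each rule is reasonable alone; together they produce an event that some patients cannot have. The patients concerned are those who functioned best in their chosen activities before surgery. They could regain full function in all eight and still be censored at 12 months as not having returned. The Introduction and the Discussion describe the aim as resumption of, or return to, daily activities, and for these patients the endpoint does not measure that.

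For the Cox model it means a subgroup that stays in the risk set throughout and contributes no events. Events are lost. The hazard ratio is pulled towards 1 and drifts over time as the patients who can have the event leave the risk set. The same outcome is also an effect measure in the Economic evaluation section, so the cost-effectiveness ratio for it inherits the problem.

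This is not detail left to an analysis plan. The article itself fixes the selection rule, the scale, the success rule and the threshold, and the difficulty follows from those four.

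**Working it through.** **1. Counting (no assumption needed).** Let k be the number of chosen activities at the best level at baseline. The number that can count is 8 − k, and the event needs 6.

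| k | can count | event possible? |
|---|---|---|
| 0 | 8 | yes |
| 1 | 7 | yes |
| 2 | 6 | only if all six improve |
| 3 | 5 | no |

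**2. The plan's sample size.** Inputs from Sample size calculation: HR 1.7, two-sided α 0.05, power 80%, ICC 0.010, 10 patients per surgeon, 50% returning, 20% dropout.

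- Freedman events: (1.96 + 0.84)² × (2.7/0.7)² ≈ 117.
- Design effect: 1 + 9 × 0.010 = 1.09.
- With the 50% read as the control arm, the intervention arm has 1 − 0.5^1.7 = 69.2%, mean 59.6%.
- N = 117/0.596 × 1.09 = 214, within 3% of the stated 220.
- Dropout: 220/0.8 = 275, or 276 as an even total.

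Other readings of the 50% lie further from 220: 245 (Schoenfeld) or 256 (Freedman) if it is the overall rate, 293 or 306 if it is the intervention arm. I therefore use the control-arm reading below. The counting in step 1 does not depend on it.

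**3. How many patients (assumed rates).** The documents give no ceiling rate. Let p be the chance that a chosen item is at the best level. The share affected is P(X ≥ 3) with X of 8 items: binomial if items are independent; beta-binomial with parameters 4p and 4(1 − p) for within-patient correlation 0.2.

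| p | independent | correlation 0.2 |
|---|---|---|
| 5% | 0.6% | 4.8% |
| 10% | 3.8% | 10.9% |
| 20% | 20.3% | 25.8% |
| 30% | 44.8% | 42.2% |

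**4. Power at 220 patients.** Power = Φ(√(E/4) × ln 1.7 − 1.96), where E is events divided by the design effect. Planned: E = 220 × 0.596/1.09 = 120.3.

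- No loss: √(120.3/4) × 0.5306 − 1.96 = 0.95, power 83%.
- 4% of events lost: E = 115.5, power 81%.
- 20% of events lost: E = 96.3, √(96.3/4) × 0.5306 − 1.96 = 0.64, power 74%.

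These figures hold the HR at 1.7 and count only the lost events.

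**5. Attenuation (illustration).** Assume exponential times, 50% control events among patients able to have the event, and 20% of patients unable to. A true HR of 1.7 is then estimated by the Cox model at about 1.59. Putting 1.59 in step 4 with E = 96.3 gives power of about 63%.

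**The case against.** **Frequency.** These are patients on a waiting list for knee arthroplasty, and the Introduction calls the burden of pain and disability in this group particularly high. Few of their chosen activities may be free of difficulty. At 5% per item only 0.6% (independent) to 4.8% (correlated) of patients are affected. This stands: the defect is certain, its frequency is not. Against that, eligibility requires paid work of at least eight hours a week, so participants retain some function.

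**Double counting.** The sample size already expects many patients not to return. If the planned 50% describes everyone, patients who cannot have the event are already among the non-returners, and scaling events down again counts them twice. This also stands. The article does not say which it is, so the power figures are conditional.

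**Improvement is intended.** Requiring a gain over baseline is a deliberate choice, illustrated with an example. That defends the one-level rule where a gain is possible. It does not defend applying the rule where no gain exists.

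**Unseen documents.** The full protocol, the eligibility appendix or the questionnaire instructions might hold a handling rule. They might, but the definition as published is complete in itself and has none.

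**A stronger reading.** A reader might infer that the rule biases the comparison between arms. The documents do not support this. The Randomization and allocation section places the baseline questionnaire before randomization, so patients with three or more top-level items should be balanced between arms. The attenuation is towards no effect.

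**Conclusion.** The point holds as a matter of counting: under the published definition, three or more top-level activities at baseline make the primary event unattainable, and two leave no margin. The consequence is lost events, an attenuated and non-proportional hazard ratio, and an endpoint that misdescribes recovery in these patients.

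Its size is unknown. Over assumed item-level rates of 5 to 30%, the affected share runs from under 1% to about 45%. For a loss of 4 to 20% of planned events, power falls from 83% to between 81% and 74%, before attenuation. That assumes the 50% refers to the control arm and did not already include these patients. It would be wrong to conclude that the trial is underpowered by a known amount: the article has no figure from which to say so. What justifies acting is that this is the sole primary endpoint, the gap is certain, and it is cheap to close.

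**What to change.** Before the unblinded analysis, amend the definition: an activity at the best level at baseline counts as returned when the patient again reports the best level after surgery; every other activity keeps the one-level rule. All eight items can then count for every patient.

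**Dating.** The day is asked only when the higher level is reached, so none is collected for these items as the article stands. Date them from the scheduled questionnaires (4 and 6 weeks, monthly to month 6, then months 9 and 12), or add the day question for these items in the remaining follow-up.

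**Reporting.** Give by arm the number of patients with three or more top-level items, which settles the unknown frequency. Keep the published definition as a sensitivity analysis.

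**Timing.** Under Blinding, researchers are blinded only during the analyses, not during data collection. The amendment should therefore be dated and registered before any outcome is examined by arm.

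**Cost.** A short change to the protocol and analysis plan with a registry update, plus a small questionnaire change if the day is to be asked. The item responses are collected anyway. The downside is that for top-level items the endpoint measures regaining baseline rather than improving on it, and dates are coarser where no day was asked.

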### Intervention

#### Development

The development of the care program under study involved various steps, including a systematic review with meta-analysis [14], focus groups with total knee arthroplasty patients [26], and a Delphi study with orthopaedic surgeons, physiotherapists, occupational physicians and a physician assistant [27] to develop the algorithms for the ikHerstel app.

Our systematic review showed that integrated care programs consisting of one or a combination of: an active referral to a case-manager, a patient tailored rehabilitation program using goal setting and/or eHealth, showed small effects on work- and/or sports participation post-surgery [14]. Moreover, previous studies by our research group showed positive effects on societal participation of integrated care programs with similar intervention elements among other patient populations, such as low back pain patients [28, 29] and gynaecological or abdominal surgery patients [30–32]. For the gynaecological and abdominal surgery patients, an eHealth intervention using the ikHerstel app was developed to support and advise them during their post-operative course. This app was previously found to be effective for returning to daily life activities, where patients in the intervention group returned to daily (work) activities 5–13 days earlier than those in the usual care group [30–32]. Because of the promising effectiveness results of the ikHerstel app, we have further developed this care program according to the wishes and preferences of knee arthroplasty patients with focus groups and an algorithm that was developed in a Delphi study [26, 27]. In the latter study, with an expert panel including orthopaedic surgeons, physiotherapists, occupational physicians and an orthopaedic physician assistant, we have developed uniform and multidisciplinary recommendations for the resumption of daily life activities after knee arthroplasty [27]. The recommendations were implemented in our smartphone ikHerstel app. Moreover, an activity tracker was linked to the ikHerstel app to enhance resumption of physical activity [33–35]. Goal attainment scaling was added to the intervention, given the promising results on satisfaction with occupational and leisure time physical activities among younger knee arthroplasty patients [36, 37].

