Pre- and postoperatively, the ikHerstel app aims to guide patients through their recovery period by providing guidance and feedback on their recovery to facilitate return to their personal daily life activities. The app consists of the following main elements:Preoperative information, with the goal to prepare the patient for their upcoming surgery and to improve recovery expectations. Previous research has concluded that the length of recovery might be reduced by having clear expectations about the recovery period and resumption of daily activities [15, 32]. The app will provide: 1) preoperative information such as a packing list and recommendations for preparations at home, 2) information about the admission day and the surgical procedure, and 3) general and practical information about the recovery period, such as commonly experienced post-operative complaints and frequently asked questions. All information will be provided in text and will be supported by short video’s (Fig.1A).Self-management and empowerment of patients by personalized perioperative recovery recommendations, developed by our research team in a Delphi study [27]. Preoperatively, patients have the opportunity to select daily life activities that are important in their daily life from a list of 26 activities. Before the surgery, patients will receive their recommendations in a personalized recovery plan with advice on when and how to resume their selected activities. Patients will discuss their recovery plan with their case-manager. Postoperatively, patients will receive these personalized recovery recommendations in the app with notifications, videos and text messages.Monitoring personal patient recovery after the surgery. Once a week, patients will complete a recovery monitor in the app. The recovery monitor is a short questionnaire in which patients answer if they have resumed (one or more of) their daily life activities. Abovementioned recovery recommendations will be personalized based on the stage of the recovery the patient is in. The underlying algorithm makes it possible to alter the patients recovery recommendations if needed throughout the recovery by distinguishing three rates of recovery: fast, average and slow. Preoperatively, patients will be categorized into one of those three recovery rates based on their recovery expectations regarding return to work (i.e., after how many days, weeks or months do patients expect to be fully back at work). Each recovery rate has its own corresponding recovery recommendations that were developed in the aforementioned Delphi study [27]. Patients who are categorized in the recovery rate ‘fast’ have more progressive recommendations as compared to patients who are categorized in the recovery rate ‘average’ and ‘slow’. Postoperatively, based on a patient's answers in the recovery monitor, a patient can shift to a faster or slower group. If patients show a delayed recovery (e.g. they can only resume < 33% of the activities that they should be able to), the algorithm will switch patients to a slower group (if not yet in the slowest group) and the patient's recovery recommendations will be altered. If patients can resume 33% to 66% of the activities they should, they remain in their group. If patients can resume 67% or more of their given recommendations, patients will switch to a faster group (if not yet in the fastest group). This allows us to provide personalized and adaptive recovery recommendations. The patient is not informed about this change (i.e. shifting to a slower or faster group), but will receive altered recommendations. The recommendations of the patient's personal recovery plan will be updated automatically every four weeks in the app, and if recommendations are adapted, a new recovery plan will be send to the patients by email.An accelerometer based activity tracker (Xiaomi Mi Band 4/6 or, if compatible, patients’ own activity tracker) will be linked to the app. Previous research has concluded that an accelerometer is a feasible instrument for measuring postoperative recovery of physical activity [33–35, 38]. The accelerometer can be worn on the wrist and will measure daily step count. Patients will be requested to wear an activity tracker from two weeks before surgery until six months after surgery to monitor their physical activity recovery and intensity levels. Four weeks after surgery, a daily step goal will be implemented in the ikHerstel app. Based on previous studies by van der Walt et al. [39], Hylkema et al. [34], Hoorntje et al. [35] and Lebleu et al. [40], we developed the following post-surgical step goals: 3000 + steps after four weeks, 4000 + steps after six weeks, 5000 + steps after eight weeks and 6000 + steps after ten weeks. Every day, patients can see their progress regarding their daily step goal and they will receive an overview of their steps once a week.Feedback on their recovery, among others by short videos in which either an orthopaedic surgeon, a physiotherapist or an occupational physician provides them with guidance on how and when best to resume activities of daily life. A dashboard will display the recovery percentage appearing after completing the weekly recovery monitor (Fig. 1B).

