### Measurements

Digital questionnaires will be administered with the Survalyzer online tool (survalyzer.com), which can be accessed through a link provided via e-mail, to assess all primary and secondary outcome parameters and additional variables at baseline, and 3, 6, 9, and 12 months after surgery. Measurements will be taken from both patients in the intervention and usual care group, regardless of whether they actually followed the intervention (when in the intervention group). The primary outcome parameter and return to work will also be measured every month during the first 6 months. Six weeks after surgery, we will also assess knee functioning (KOOS), pain (VAS), quality of life (EQ-5D-5L) and patient satisfaction. Table 4 shows an overview of our outcome measures, measurement instruments and measurement moments. All relevant costs will be measured using online cost-questionnaires administered at baseline, 3, 6, 9, and 12 months post-surgery.

**Table 4 Tab4:** Outcome measures, measurement instruments and measurement moments

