*** Process***										
***Patient Satisfaction***			X					X		

T_0_ = baseline, ± 6–8 weeks before surgery; T_1_ = 4 weeks after surgery; T_2_ = 6 weeks after surgery; T_3_ = 2 months after surgery; T_4_ = 3 months after surgery; T_5_ = 4 months after surgery; T_6_ = 5 months after surgery; T_7_ = 6 months after surgery; T_8_ = 9 months after surgery; T_9_ = 12 months after surgery

Patients will have two weeks to complete the questionnaire. After approximately one week, a reminder will be sent by e-mail. If after two weeks the questionnaire is not yet completed, an attempt will be made to contact the patient by phone to encourage them to still complete the questionnaire.

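### The primary event date is a recalled day, and only the intervention arm has a weekly resumption record and a dated plan, so dating may differ by arm; time the event on the questionnaire grid

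*Protocol article*

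**What the plan says.** The Outcomes section defines the primary outcome as the "time since surgery to resume six out of the selected eight activities of their own quality of life short form". An activity counts once its difficulty rating is at least one level better than at baseline. The rule for the date is: "If patients reach this level, they will be asked at what day they reached this level". The Effect analysis section puts the resulting time into a multilevel Cox model.

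Both arms get the same questionnaires (Measurements: "Measurements will be taken from both patients in the intervention and usual care group"). On timing, that section says "The primary outcome parameter and return to work will also be measured every month during the first 6 months". The footnote to Table 4 gives the full grid: 4 and 6 weeks, then 2, 3, 4, 5 and 6 months, ending with "T_8_ = 9 months after surgery; T_9_ = 12 months after surgery".

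The app described under Component 1 belongs to the intervention arm only. There, "Once a week, patients will complete a recovery monitor in the app", which is a "short questionnaire in which patients answer if they have resumed (one or more of) their daily life activities". The same patients see a recovery percentage and hold a personal plan advising when each chosen activity can be taken up again. The Usual care section says that control eHealth does not concern itself with return to daily activities.

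On earlier evidence for the app, the Development section reports that "patients in the intervention group returned to daily (work) activities 5–13 days earlier than those in the usual care group", in gynaecological and abdominal surgery. Strengths and limitations does not mention recall of the event date.

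**The concern.** The event time is a remembered day, and the two arms remember it under different conditions. An intervention patient has been asked every week about resumed activities and has a plan with target times. A control patient has only the questionnaires. If controls who cannot place the day tend to give the day on which they are asked, their events are dated late. If intervention patients tend to give the date in their plan, their events are moved as well, in a direction that cannot be known beforehand.

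This would be a difference in measurement between arms. Blinding does not remove it, because the memory aid works whether or not patients know their allocation. Late dating in controls looks like slower recovery and would push the HR above 1, the direction of the trial's hypothesis.

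**Working it through.** **Inputs from the protocol.** The questionnaire grid (Table 4); 220 patients to observe, taken as 110 per arm (Sample size calculation, 1:1 allocation); 12 months of follow-up; planned HR 1.7. The protocol states no figure for dating error, so there is none to reproduce.

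**Step 1: gaps.** In days after surgery the grid is about 0, 28, 42, 61, 91, 122, 152, 183, 274, 365. The differences are 28, 14, 19, 30, 31, 30, 31, 91, 91. Recall over about three months therefore arises only after month 6. Under the distributions in Step 2, 13-41% of events fall there.

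**Step 2: shift if a control gives the questionnaire day (assumption).** The mean delay is 19.1 days (Weibull shape 1.5, median 90 days), 25.1 days (exponential, median 180) or 27.4 days (exponential, median 365). If half of controls do this, the mean arm difference is half of that: 0.5 × 19.1 = 9.6 to 0.5 × 27.4 = 13.7 days. That is of the order of the cited 5-13 days. For scale, the planned HR of 1.7 under exponential times corresponds to a median difference of m − m/1.7, which is 37, 74 and 150 days for m = 90, 180 and 365.

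**Step 3: effect on the HR with no true effect.** Simulated Cox analyses used 110 per arm, censoring at 365 days, exact dates in the intervention arm and 500 to 1,000 runs per setting. Monte Carlo error of the rejection rates is about 1-2 points. Each patient has a single event time, whereas the real endpoint is the sixth of eight recalled dates.

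| Control dating (assumed) | Event times | HR | Two-sided rejection at 0.05 |
|---|---|---|---|
| Random within the true gap | all three of Step 2 | 1.00-1.03 | about 5% |
| Half give questionnaire day | exponential, medians 365 to 90 | 1.02-1.10 | about 5-10% |
| Half give questionnaire day | Weibull shape 1.5 | 1.04-1.16 | 7-18% |
| All give questionnaire day | exponential, medians 365 to 90 | 1.07-1.25 | about 4-39% |
| All give questionnaire day | Weibull shape 1.5 | 1.12-1.37 | 6-64% |

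The same error in both arms leaves the HR at about 1.00.

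**Step 4: how much is tie handling.** These runs used the Breslow approximation, and heaped dates create ties in one arm only. Midpoint dating by controls has a mean signed error of only 0.6 to 1.4 days, yet gave HRs of 1.03-1.12, so part of the inflation comes from the ties. Repeating the runs with Efron's method (500 runs; medians 90, 180 and 365; shapes 1 and 1.5) gave about 1.03-1.13 for half and 1.04-1.26 for all. The direction is the same and the upper ends are lower.

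**Step 5: does the grid analysis cure it?** In the same settings a complementary log-log model on the common grid gave null HRs of 0.97-1.01 with rejection of about 5%. At a true HR of 1.7, power on the grid and with exact days was 98% and 98%, 94% and 94%, 87% and 87%. The standard error was at most about 2% larger.

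**The case against.** The strongest objection is that nothing in the protocol shows that dating differs by arm. A questionnaire gap caps the error within an interval. It is not a difference between arms, and both arms have the same gaps. The weekly monitor is also not a diary of the endpoint. It covers activities chosen from the app's list of 26, while the endpoint needs a one-level gain on six of eight items chosen from a separate list of 29. App use has no required minimum, and no section uses monitor entries to set the primary date. Inflation also depends on the intervention arm dating well: if a quarter of intervention patients also give the questionnaire day, the half-of-controls result under exponential times falls to HR 1.02-1.04 with 3-6% rejection. Finally, sensitivity analyses are promised, and their detail may sit in an analysis plan that is not shown.

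Most of this stands, and it limits the claim. A reader might infer that dating accuracy does differ by arm, and by more than the app's earlier effect. The documents do not support that: size and direction are unknown, the 5-13 days come from other surgical populations, and this trial is planned on HR 1.7. It would equally be wrong to infer that intervention patients can date events to the week, or that three-month recall is typical.

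What the objection does not remove is that the protocol itself fixes the recalled day as the event time, and that the intervention contains an aid, if an indirect one, to recalling when activities were resumed. A promise of unspecified sensitivity analyses does not deal with that.

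**Conclusion.** The point holds as a risk to the primary endpoint, not as a demonstrated bias. Dating of the event may differ by arm, patient blinding does not prevent this, and the protocol does not address it. Random error in one arm is nearly harmless. A one-sided shift is not: if half of controls give the questionnaire day, the null HR is about 1.02-1.16, and if all do, about 1.07-1.37, with type I error from near nominal to well above 5%.

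These ranges rest on the assumed share of controls, exact dating in the intervention arm, the assumed event-time distribution and Breslow ties; Efron's method lowers the upper ends. They are neither estimates nor bounds. The gaps are wide enough to allow a shift of the order of 5-13 days, and no more than that can be said. Because the remedy uses data already planned, the change is worth making. Confidence is medium.

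**What to change.** Prespecify an analysis that places each event between the last questionnaire not meeting the six-of-eight rule and the first one meeting it. Use actual completion dates, since patients have two weeks to respond and are then telephoned. Fit an interval-censored or discrete-time (complementary log-log) proportional hazards model and retain surgeon clustering. State how an activity counts if its level later falls back, so that the endpoint stays the intended one.

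Preferably make this the primary analysis, with the recalled-day Cox model as sensitivity analysis. At minimum, name it as a sensitivity analysis reported beside the recalled-day result. State that app monitor entries will not be used to set or correct the date, and name the method for ties in the Cox model.

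The cost is wording only: functioning levels are already collected at every questionnaire in both arms. Day-level information is given up in the grid analysis, for a standard error at most about 2% larger in simulation. The change does not remove any arm difference in how patients report their functioning level.
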